**Section E2: Step 1: Behavioural Measurements –Alcohol Consumption**

***The next questions ask about the consumption of alcohol.***

| **Q-Number** | **Question** | **Response** | **Code** |
| --- | --- | --- | --- |
| 68. | Have you **ever** consumed an alcoholic drink such as beer, wine, spirits, fermented cider or *[add other local examples]*?  *(USE SHOWCARD OR SHOW EXAMPLES)*   1. Yes 2. No |  | Qn68 |
| 69. | Have you consumed an alcoholic drink within the **past 12 months**?  Yes 2. No |  | Qn69 |
| 70. | During the past 12 months, **how frequently** have you had at least one alcoholic drink? *(READ RESPONSES, USE SHOWCARD)*  1 .Daily  2. 5-6 days per week  3. 1-4 days per week  4. 1-3 days per month  5. Less than once a month |  | Qn70 |
| 71. | Have you consumed an alcoholic drink within the **past 30 days**?  Yes 2. No |  | Qn71 |
| 72. | During the past 30 days, on how many **occasions** did you have at least one alcoholic drink?  Number _______________Don't know 77 |  | Qn72 |
| 73. | During the past 30 days, when you drank alcohol, **on average**, how many **standard alcoholic drinks** did you have during one drinking occasion?*(USE SHOWCARD)*  Number _______________Don't know 77 |  | Qn73 |
| 74. | During the past 30 days, what was the **largest number** of standard alcoholic drinks you had on a single occasion, counting all types of alcoholic drinks together? |  | Qn74 |
| 75. | During the past 30 days, how many times did you have for **men**: **five or more** for **women**: **four or more** standard alcoholic drinks in a single drinking occasion? |  | Qn75 |

**Section E3: Step 1: Behavioural Measurements –Diet**

***The next questions ask about the fruits and vegetables that you usually eat. I have a nutrition card here that shows you some examples of local fruits and vegetables. Each picture represents the size of a serving. As you answer these questions please think of a typical week in the last year.***

| **Q-Number** | **Question** | **Response** | **Code** |
| --- | --- | --- | --- |
| 76. | In a typical week, on how many days do you **eat fruit**? *If Zero days, skip*  Number of days____________________Don't Know 77 |  | Qn76 |
| 77. | How many **servings** of fruit do you eat on **one** of those days? (*USE SHOWCARD) If Zero days, skip*  Number of days___________________Don't Know 77 |  | Qn77 |
| 78. | In a typical week, on how many days do you **eat vegetables**?*(USE SHOWCARD) If Zero days, skip*  Number of days___________________Don't Know 77 |  | Qn78 |
| 79. | How many **servings** of vegetables do you eat on one of those days? *(USE SHOWCARD) If Zero days, skip*  Number of days____________________Don't Know 77 |  | Qn79 |
| 80. | What type of **oil or fat is most often** used for meal preparation in your household?*(USE SHOWCARD)* *(SELECT ONLY ONE)*   1. Animal Oil 2. Vegetable oil 3. Both(mixed) 4. DK |  | Qn80 |
| 81. | On average, how many meals per week do you eat that were not prepared at a home? By meal, I mean breakfast, lunch and dinner.  Number of days____________________Don't Know 77 |  | Qn81 |
| 82. | Do you add salt when you eating some food?   1. Yes 2. No |  | Qn82 |

**Section E4: Step 1: Behavioural Measurements –Physical activities**

Next I am going to ask you about the time you spend doing different types of physical activity in a typical week. Please answer these questions even if you do not consider yourself to be a physically active person. Think first about the time you spend doing work. Think of work as the things that you have to do such as paid or unpaid work, study/training, household chores, harvesting food/crops, fishing or hunting for food, seeking employment*.* In answering the following questions 'vigorous-intensity activities' are activities that require hard physical effort and cause large increases in breathing or heart rate, 'moderate-intensity activities' are activities that require moderate physical effort and cause small increases in breathing or heart rate.

| **Q-Number** | **Question** | **Response** | **Code** |
| --- | --- | --- | --- |
| **Work Related Activities** | | | |
| 83. | Does your work involve vigorous-intensity activity that causes large increases in breathing or heart rate like lifting heavy loads, manual construction work, digging etc for at least 10 minutes continuously? *USE SHOWCARD)*   1. Yes 2. No |  | Qn83 |
| 84. | In a typical week, on how many days do you do vigorous-intensity activities as part of your work? Number of days________________________ |  | Qn84 |
| 85. | How much time do you spend doing vigorous-intensity activities at work on a typical day? | a) Hours : ___  b)Minutes:___ | Qn85a  Qn85b |
| 86. | Does your work involve moderate-intensity activity, that causes small increases in breathing or heart rate such as brisk walking*, carrying light loads, doing chores like cleaning, washing or ironing clothes etc ,*for at least 10 minutes continuously?   1. Yes 2. No |  | Qn86 |
| 87. | In a typical week, on how many days do you do moderate-intensity activities as part of your work?  Number of days________________________ |  | Qn87 |
| 88. | How much time do you spend doing moderate-intensity activities at work on a typical day? | a) Hours : ___  b)Minutes:___ | Qn88a  Qn88b |
| **Travel to and from place** | | | |
| The next questions exclude the physical activities at work that you have already mentioned.  Now I would like to ask you about the usual way you travel to and from places. For example to work, for shopping, to market, to place of worship. | | | |
| **Q-Number** | **Question** | **Response** | **Code** |
| 89. | Do you walk or use a bicycle *(pedal cycle)* for at least 10 minutes continuously to get to and from places?   1. Yes 2. No |  | Qn89 |
| 90. | In a typical week, on how many days do you walk or bicycle for at least 10 minutes continuously to get to and from places?  Number of days________________________ |  | Qn90 |
| 91. | How much time do you spend walking or bicycling for travel on a typical day? | a) Hours : ___  b)Minutes:___ | Qn91a  Qn91b |
| **Recreational activities** | | | |
| The next questions exclude the work and transport activities that you have already mentioned.  Now I would like to ask you about sports, fitness and recreational activities (leisure), *[Insert relevant terms]*. | | | |
| **Q-Number** | **Question** | **Response** | **Code** |
| 92. | Do you do any vigorous-intensity sports, fitness or recreational *(leisure)* activities that cause large increases in breathing or heart rate like *running, playing football etc,* for at least 10 minutes continuously?  *(USE SHOWCARD)*   1. Yes 2. No |  | Qn92 |
| 93. | In a typical week, on how many days do you do vigorous-intensity sports, fitness or recreational *(leisure)* activities?  Number of days________________________ |  | Qn93 |
| 94. | How much time do you spend doing vigorous-intensity sports, fitness or recreational activities on a typical day? | a) Hours : ___  b)Minutes:___ | Qn94a  Qn94b |
| 95. | Do you do any moderate-intensity sports, fitness or recreational *(leisure)* activities that cause a small increase in breathing or heart rate such as brisk walking*, cycling, swimming, dancing* etc for at least 10 minutes continuously?   1. Yes 2. No |  | Qn95 |
| 96. | In a typical week, on how many days do you do moderate-intensity sports, fitness or recreational *(leisure)* activities?  Number of days________________________ |  | Qn96 |
| 97. | How much time do you spend doing moderate-intensity sports, fitness or recreational *(leisure)* activities on a typical day? | a) Hours : ___  b)Minutes:___ | Qn97a  Qn97b |
| **Sedentary behaviour** | | | |
| The following question is about sitting or reclining at work, at home, getting to and from places, or with friends including time spent sitting at a desk, sitting with friends, travelling in car, bus, train, reading, playing cards or watching television, but do not include time spent sleeping.  *(USE SHOWCARD)* | | | |
| 98. | How much time do you usually spend sitting or reclining on a typical day? | a) Hours : ___  b)Minutes:___ | Qn98a  Qn98b |

**Section E6: Step 1: Familial –Hypertension**

| **Q-Number** | **Question** | **Response** | **Code** |
| --- | --- | --- | --- |
| 99. | Have you ever had your blood pressure measured by a doctor or other health worker? 1. Yes 2. No |  | Qn99 |
| 100. | Have you ever been told by a doctor or other health worker that you have raised blood pressure or hypertension? 1. Yes 2. No |  | Qn100 |
| 101. | Have you been told in the past 12 months? 1. Yes 2. No |  | Qn101 |

**Section E7: Step 1: Familial –Diabetes**

| **Q-Number** | **Question** | **Response** | **Code** |
| --- | --- | --- | --- |
| 102. | Have you ever had your blood sugar measured by a doctor or other health worker? 1. Yes 2. No |  | Qn102 |
| 103. | Have you ever been told by a doctor or other health worker that you have raised blood sugar or diabetes? 1. Yes 2. No |  | Qn103 |
| 104. | Have you been told in the past 12 months? 1. Yes 2. No |  | Qn104 |

**Section F: Step 2 Physical Measurements**

| **Q-Number** | **Question** | **Response** | **Code** |
| --- | --- | --- | --- |
| **Height and weight** | | | |
| 105. | Device IDs for height and weight | a)Weight:_____ | Qn105a |
|  |  | b) Height:______ | Qn105b |
| 106. | Height (cm) | ______.____ | Qn106 |
| 107. | Weight (kgs) | ______.____ | Qn107 |
| **Waist Circumference** | | | |
| 108. | Device ID for waist | ___________ | Qn108 |
| 109. | Waist circumference (cm) | ______.____ | Qn109 |
| **Blood Pressure** | | | |
| 110. | Device ID for blood pressure |  | Qn110 |
| 111. | Cuff size used: 1. Small 2. Medium 3. Larger |  | Qn111 |
| 112. | Reading 1 a) Systolic ( mmHg) | __________ | Qn112a |
|  | b)Diastolic (mmHg) | __________ | Qn112b |
| 113. | Reading 2 a) Systolic ( mmHg) | __________ | Qn113a |
|  | b)Diastolic (mmHg) | __________ | Qn113b |
| 114. | Reading 3 a) Systolic ( mmHg) | __________ | Qn114a |
|  | b)Diastolic (mmHg) | __________ | Qn114b |
| 115. | During the past two weeks, have you been treated for raised blood pressure with drugs (medication) prescribed by a doctor or other health worker?   1. Yes 2. No |  | Qn115 |
| **Hip Circumference** | | | |
| 116. | Hip circumference (cm) | __________ | Qn116 |

**Section G: Step 3 Biochemical Measurements**

| **Q-Number** | **Question** | **Response** | **Code** |
| --- | --- | --- | --- |
| **Blood Glucose** | | | |
| 117. | During the past 12 hours have you had anything to eat or drink, other than water? 1. Yes 2. No |  | Qn117 |
| 118. | Technician names (initials) | ___________ | Qn118 |
| 119. | Device ID | ___________ | Qn119 |
| 120. | Time of day blood specimen taken (24 hour clock) | Hours :  minutes | Qn120 |
| 121. | Fasting blood glucose: *(mmol/l)* |  | Qn121 |
| 122. | Today, have you taken insulin or other drugs (medication) that have been prescribed by a doctor or other health worker for raised blood glucose?  1. Yes 2. No |  | Qn122 |

| **Q-Number** | **Question** | **Response** | **Code** |
| --- | --- | --- | --- |
| **Blood Lipids** | | | |
| 123. | Device ID |  | Qn123 |
| 124. | Total cholesterol *(mmol/l)* |  | Qn124 |
| 125. | During the past two weeks, have you been treated for raised cholesterol with drugs (medication) prescribed by a doctor or other 1. Yes 2. No |  | Qn125 |
| 126. | Triglycerides  *(mmol/l)* |  | Qn126 |
| 127. | During the past two weeks, have you been treated for raised Triglycerides with drugs (medication) prescribed by a doctor or other 1. Yes 2. No |  | Qn127 |
| 128. | High Density Lipoprotein *(mmol/l)* |  | Qn128 |
| 129. | During the past two weeks, have you been treated for low High Density Lipoprotein s with drugs (medication) prescribed by a doctor or other 1. Yes 2. No |  | Qn129 |
| 130. | Low Density Lipoprotein *mmol/l)* |  | Qn130 |
| 131. | During the past two weeks, have you been treated for raised Low Density Lipoprotein with drugs (medication) prescribed by a doctor or other  1. Yes 2. No |  | Qn131 |

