2.6.1 Magnitude of type2 diabetes, behaviourial and its risk factors: The prevalence of type 2 diabetes among urban street cooked food consumers will be determined. A person will be considered to have diabetes if the reading for fasting blood glucose measured using Accu-check machine is >7.0mmol/L or is on medication for raised blood glucose. This study will also assess the prevalence metabolic and behavioural risk factors of type 2 diabetes. Prevalence of metabolic risk factors will be assessed as follow: being overweight or obese (BIM≥25Kg/M^2^), raised TC (≥5.1mmol/L), raised TG (≥2 mmol/L), low HDL (<1.03 mmol/l for Male and < 1.29 for Female), raised LDL (>2.6 mmol/L), Abnormal Waist Hips Ratio for male and female if the value is >0.8 and >0.9 respectively, raised Systolic BP (≥140mmHg) and Diastolic BP (≥90 mmHg) (17,18). Behaviorial assessement will including participating in physical activities as per recommended standard (≥600MET/week), Behaviourial assessment will include consumption of fruits and vegetables as per standard (≥5 days per week), non-harmful drinking (5 or less for male and 4 or less for female units of alcohol per week) and not consuming table salt will be assessed (18,52).

**Blood Pressure (BP) Measurements**: Blood pressure will be measured while patients are in a sitting position, using an M4 Omron® device. An average of the last two readings taken three times consistently after three minutes from the left arm will be treated as final reading and will be used during analysis(18). The final will be classified as raised blood pressure if BP of ≥140/90mmHg.

**Weight Measurement**: SECA® weighing scale will be used to measure weight. Participant will be asked to remove any heavy clothing (such as coats and shoes) and stand still on the weighing scale, with hands by their sides.

**Height Measurement:** Height will be measured with a SECA® stadiometer, while a patient is facing directly ahead. Patients will be instructed to remove their shoes, caps or head scarf, keep their feet together, and stand with their arms by the sides. Measurement will be taken with heels, buttocks and upper back in contact with the stadiometer.

**Body Mass Index (BMI):** The product of weight (in Kilograms) divided by height squared (m^2^) will give BMI. Categorization BMI will be as follows ; obesity is ≥30 kg/m2; Overweight if the BMI is > 25 but < 30kg/m2, and normal if the BMI is between 18-25kg/m2 and underweight if below 19 kg/m^2^ (53).

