**Waist circumference:** The measurement will be done according to WHO guidelines where by measurement will be taken at the approximate midpoint between the lower margin of the last palpable rib and the top of the iliac crest (54). The values will be grouped as follows abnormal waist circumference of male and female are >94 cm and >80 cm respectively ; this classification is according to World Health Organizations (WHO) and International Diabetes Federation (IDF) recommendations(1,3).

**Hips measurements:** Hip measurement is one of an important parameter for monitoring weight gain or loss. Participant will be asked to remove heavy garments and put the feet together then soft measuring tape will wrapped and snag around the widest part of his/her hips. Then the value of hip measurement is the point at which the end of the tape meets the remaining length.

**Waist Hips Ratio**: Waist to hip ratio is a measure of how fat is distributed around the body. It is calculated by dividing waist to hips values. Waist Hips Ratio will be considered normal for male and female if the value is ≤0.8 and ≤0.9 respectively(55).

**Laboratory Tests**: Study participants will be requested to return to the clinics to provide fasting blood samples for blood glucose and lipid profile (TC, HDL and Triglyceride) tests in the following day after fasting for at least 8 hours. The tests will be performed by trained laboratory technicians.

**Fasting Blood Glucose:** Blood sample will be taken by finger prick (capillary) and measured using Accu-check machine. Raised fasting blood glucose will be considered if the result is >7.0mmol/L (19,20)**.**

**Lipid profile testing:** Blood sample will be collected for testing HDL-C, HDL-C, TC, and TG-C. Blood will be kept at room temperature and will be analyzed the same day using fully automated biochemistry analyzers by the direct end point enzymatic method.

**Alcohol drinking**: Participants will be interviewed on the history of alcohol drinking and those who will be found currently drinking will be asked further questions. These questions will include age when started drinking, frequency of drinking and amount taken on average when they drink.

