2.6.4 Effectiveness of intervention package in reducing type2 diabetes risk factors: At the end of an intervention the mean comparison using independent T-test of all metabolic risk factors for T2DM will be made between the control and intervention groups. For pre-post analysis, the study will apply Generalized Linear Mixed Models (GLMM) to accommodate fixed and random variables. Sensitivity analysis will be conducted to assess if variables which will be statistically significant by GLMM model, will be consistently significant using the Bayesian Modelling technique with Markov Chain Monte Carlo (MCMC). Post and baseline analysis will also employ both linear and logistic regression to assess the factors associated with both primary and secondary outcome of interest. The following are the metabolic risk factors which will be assessed: High Density Lipoprotein Cholesterol (HDL-C), Low Density Lipoprotein Cholesterol (LDL-C), Total Cholesterol (TC), and triglycerides Cholesterol (TG-C) Body mass index (BMI), Waist Hips Ratio (WHR) and Blood Pressure (BP) (4,5,22,23,47,49), these will be our primary outcome of interest. The study will also assess mean knowledge and attitude scores as our secondary outcomes, mean days of fruits/vegetable consumption per week, mean number of cigarettes smoked per week, drinks consumed per week and mean MET/week between the control and intervention sites. Frequency of alcohol consumption and smoking will be also compared between the control and intervention sites. Lastly, the study will also compare the proportion of quitting alcohol consumption and smoking tobacco products between the control and intervention sites.

2.6.5 Develop a model for predicting metabolic risk factors for type2 diabetes: After collecting the endline data then a model will be developed using Multivariate/Joint Bayesian techniques to assess socio-economic and behavirioal risk factors which influence each metabolic risk factors and those which influence these factors jointly. **Table 4** below shows the type of predictive/explanatory factors which will be modelled per each metabolic risk factor of T2DM(16).

Table 4 Dependent and independent variables

| **Dependent variables- Metabolic Risk factors of T2DM** | **Independent variables/confounders** |
| --- | --- |

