2.7.2 Plate Model: Before implementing the food plate model the consumers and vendors who will consent to be recruited for the intervention arm will be educated on how to prepare the standard and recommended food plate model and its hypothesized role of reducing metabolic risk factors of T2DM. We envisaged that knowledge about the current topic will influence practice and increase uptake of an intervention. The benefits of serving the food plate model will be explained to the vendors and these benefits will include serving small amount of carbohydrate, getting extra business by selling separate portion of vegetables and fruits after the project implementation thus getting more profit. For the consumers the benefits of plate model will include paying reduced price for carbohydrate since amount to be served will be the quarter of the normal served amount. Other advantages will include preventing the consumers from excess weight gain and contributing to balancing lipid T2DM metabolic risk factors. More emphasize will be given to the participants regarding the recommended ratio of fruits, vegetables, fats/protein and carbohydrate. Participants will be also instructed on how to ensure that the food plate model contain the recommended amount of potassium, magnesium and calcium levels. The food plate model will consists of more fruits and vegetables which will be half normal eaten plate before the intervention and each quarter will comprise carbohydrate and fats/protein. The participants will be insisted to avoid diary with high saturated fats and cholesterol.

2.8 Project monitoring: To ensure sustainability of the outcomes; the project will involve municipals officers during the implementation of the study so that they take lead in promoting supply and consumption of healthy diet. Intervention program will take three months(57). Monitoring will be done to ensure adherence and compliance as per study protocol requirements. This will involve signing a daily healthy plate form and weekly visits (intervention arm) while a daily lunch form and weekly visit (control arm). The main targets indicators will include mean of metabolic components (systolic and diastolic blood pressure, fasting blood glucose, body mass index, waist circumference, triglycerides and high density lipoprotein), proportion of respondents with high knowledge and positive attitude before and after intervention.

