**Sehemu G: Step 3 Vipimo vya mwili vinavyohusisha kutoa damu**

| **Sukari katika Damu** | | | |
| --- | --- | --- | --- |
| 117. | Ndani ya masaa 12 yaliyopita, umekula au kunywa kitu chochote zaidi ya maji?  1. Ndiyo 2. Hapana |  | B1 |
| 118. | Majina ya mpimaji (vifupi) | ___________ | Qn117 |
| 119. | Utambulisho wa kifaa cha kupimia | ___________ | Qn118 |
| 120. | Muda kipimo kilipochukuliwa (kwa masaa 24) | a)Masaa______  b)Dakika______ | Qn119 |
| 121. | Kiwango cha sukari katika damu kabla ya kula: *(mmol/l)* |  | Qn120 |
| 122. | Kwa siku ya leo, je umetumia dawa yeyote ya kisukari uliyopewa na mtumishi wa afya kama insulin au vidonge vya kushusha sukari?  1. Ndiyo 2. Hapana |  | Qn121 |

| **Namba ya swali** | **Swali** | **Jibu** | **Code** |
| --- | --- | --- | --- |
| **Mafuta katika damu** | | | |
| 123. | Utambulisho wa Mpimaji |  | Qn123 |
| 124. | Lehemu *(TC) (mmol/l)* |  | Qn124 |
| 125. | Katika wiki mbili zilizopita, je umetumia dawa yeyote ya vidonge uliyopewa na mtumishi wa afya vya kushusha kiasi cha lehemu kwenye damu?  1. Ndiyo 2. Hapana |  | Qn125 |
| 126. | Triglycerides  *(mmol/l)* |  | Qn126 |
| 127. | Katika wiki mbili zilizopita, je umetumia dawa yeyote ya vidonge uliyopewa na mtumishi wa afya vya kushusha kiasi cha Triglycerides kwenye damu?  1. Ndiyo 2. Hapana |  | Qn127 |
| 128. | High Density Lipoprotein *(mmol/l)* |  | Qn128 |
| 129. | Katika wiki mbili zilizopita, je umetumia dawa yeyote ya vidonge uliyopewa na mtumishi wa afya vya kushusha kiasi cha High Density Lipoprotein kwenye damu?  1. Ndiyo 2. Hapana |  | Qn129 |
| 130. | Low Density Lipoprotein *mmol/l)* |  | Qn130 |
| 131. | Katika wiki mbili zilizopita, je umetumia dawa yeyote ya vidonge uliyopewa na mtumishi wa afya vya kushusha kiasi cha Low Density Lipoprotein kwenye damu?  1. Ndiyo 2. Hapana |  | Qn131 |

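### The protocol asks for a fast of at least 8 hours, but the only fasting item looks back 12 hours, so a 'Yes' answer mixes compliant and non-fasting samples

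*Protocol*

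**What the plan says.** Section 2.6.1 of the protocol (Laboratory Tests) has participants come back to give blood for glucose and lipid "tests in the following day after fasting for at least 8 hours".

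Appendix B, Section G, holds the form for those samples. Its one fasting item, Qn117, is answered yes or no: "During the past 12 hours have you had anything to eat or drink, other than water". The Swahili form (Sehemu G, item 117) keeps the 12-hour window: "Ndani ya masaa 12 yaliyopita, umekula au kunywa kitu chochote zaidi ya maji". The only related time item is Qn120, "Time of day blood specimen taken (24 hour clock"; no item asks when the participant last ate or drank. At the end-term evaluation the whole form is used again with additions, so the same item serves both time points.

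The measurements concerned are used as follows:

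- Section 2.6.4 lists triglycerides and the other lipids among the outcomes of which it says "these will be our primary outcome of interest".
- Section 2.8 names "fasting blood glucose, body mass index, waist circumference, triglycerides and high density lipoprotein" among the main target indicators.
- Section 2.6.1 states: "A person will be considered to have diabetes if the reading for fasting blood glucose measured using Accu-check machine is >7.0mmol/L", or if the person is on medication for raised blood glucose.
- Table 1 gives fasting glucose its own sample-size row (4.8 to 4.3 mmol/L), and Table 4 makes it a dependent variable of the prediction model.

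**The concern.** A fasting check should show whether the protocol's fasting condition was met. This one tests a longer window than the condition it is meant to verify. Someone who kept to the 8-hour instruction but ate 10 hours before the sample has to answer 'Yes', exactly like someone who ate 3 hours before.

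Whoever analyses the data then has two poor options. Treating every 'Yes' as non-fasting drops samples that satisfy the protocol. Keeping every 'Yes' lets in samples that do not, with nothing to mark which they are. Triglycerides, a listed primary outcome, and fasting glucose, which defines diabetes prevalence, are the measurements at stake.

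This cannot be left to a statistical analysis plan. Such a plan can say how to treat a 'Yes', but it cannot reconstruct a last-meal time that the form never asked for.

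**Working it through.** The protocol gives no figure to reproduce here. The check sets the instruction beside the form item and works out the answer for each length of fast.

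**Inputs.** Required fast: at least 8 hours (section 2.6.1). Look-back of Qn117: 12 hours (Appendix B, Section G, and Swahili item 117). Clock time of the specimen: recorded. Time of last intake: not recorded.

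**Answer by true hours since last intake, assuming truthful replies.**

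| Hours since last intake | Meets the 8-hour instruction? | Answer to Qn117 |
| --- | --- | --- |
| under 8 | no | Yes |
| 8 to under 12 | yes | Yes |
| 12 or more | yes | No |

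The first two rows share an answer. With a 07:00 sample, last intake at 22:00 is a fast of 9 hours and complies; last intake at 06:00 is a fast of 1 hour and does not. Both are recorded as 'Yes' with a specimen time of 07:00. The third row is clean: every 'No' meets the instruction.

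**How many compliant participants would answer 'Yes'?** For a sample at time T, these are the people whose last intake fell after T minus 12 hours and no later than T minus 8 hours. The documents give neither meal times nor sampling times, so the cases below are assumptions, with last intake spread evenly over the stated window:

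- Sample 09:00, last intake 18:00–21:00. Band: after 21:00. Share 0/3 = 0%.
- Sample 08:00, last intake 18:00–22:00. Band: after 20:00. Share 2/4 = 50%.
- Sample 08:00, last intake 19:00–23:00. Band: after 20:00. Share 3/4 = 75%.
- Sample 07:00, last intake 19:00–23:00. Band: after 19:00. Share 4/4 = 100%.

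Equally plausible choices cover the whole range from 0% to 100%. None of these cases contains a non-faster, so they show only how far the 'Yes' group could fill with compliant people, not how many samples are invalid.

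**Codes on the Swahili form.** The fasting question, item 117, carries the code B1, and Qn117 is attached to the technician's initials (item 118). The shift continues: the specimen time (item 120) is coded Qn119, and the glucose reading (item 121) is coded Qn120. At data entry the fasting answer could be lost or confused with another field.

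**The case against.** The best defence is that Qn117 is stricter than the instruction rather than opposed to it. If answers are truthful, every non-faster is in the 'Yes' group, so an analysis restricted to 'No' answers would be free of non-fasting samples. That stands. A reader might infer that the item says nothing about fasting, or that non-fasting values leave no trace at all; neither follows. What remains is that the 'No'-only analysis gives up an unknown number of compliant samples, and the 'Yes' group cannot be divided.

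A second defence is that the form is the same in both arms and both rounds, so equal fast-breaking with a similar effect would largely cancel in a comparison of means. This also stands. A reader might go further and compute a bias: if non-fasting readings ran 1–2 mmol/L higher and undetected fast-breaking differed by 10 percentage points between arms, the shift would be 0.10 × 1 to 0.10 × 2 = 0.1–0.2 mmol/L, or 20–40% of the 0.5 mmol/L glucose target (4.8 − 4.3). Only that target comes from the protocol. The rise and the imbalance are invented, and fast-breaking, not the wording of Qn117, would cause the shift. Nor do the documents support supposing that participants are food traders prone to break the fast, since the metabolic outcomes are measured in consumers.

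Third, the reach is limited. Waist-hip ratio, which set the sample size, is untouched by fasting, as are BMI and blood pressure, and fasting glucose is not in the primary list of section 2.6.4.

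Last, section 2.6 says the tool was adapted from the WHO STEP questionnaire and other studies, so comparability might be a reason to keep an inherited item. The protocol does not say where this item came from or give that reason, and inheritance would not reconcile 12 hours with this protocol's 8.

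**Conclusion.** The mismatch is certain and is present in both language versions. The trial cannot verify its own fasting criterion for anyone who answers 'Yes', and analysis cannot repair this afterwards. The conclusion assumes only truthful answers.

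The practical size is unknown. It depends on the share of participants fasting 8 to under 12 hours, anywhere from 0% to 100% under assumed timings, and on the number who broke the fast, for which the documents give no figure. No bias in the arm comparison has been shown. This is a specific, correctable fault in data capture that affects a listed primary outcome and the diabetes classification; it does not put the trial's main conclusion in doubt.

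**What to change.** Reconcile the instruction and the form before data are collected.

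1. In both languages, replace Qn117 with the date and time of last food or drink other than water. Hours fasted is then the specimen time (English Qn120) minus that time. Qn120 holds a clock time only and sampling falls on the day after the first visit, so record the specimen date beside it.
2. At minimum, change the look-back in both forms to the protocol's own 8 hours. This avoids recalling a clock time, but yields only a yes/no answer.
3. On the Swahili form, replace code B1 with Qn117 and correct the shifted codes of items 118 to 122, so that the two versions merge.
4. Check the answer before drawing blood and rebook where the protocol's fast was not met, in the same way in both arms and at both time points.
5. Keep all randomised participants in the main analysis and use fasting status for a sensitivity analysis. Excluding values after randomisation could itself bias the comparison if fast-breaking differed by arm.

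The cost is one reworded item and a few corrected codes, a slight recall burden, and some rebooked visits, whose number the documents do not allow one to predict.
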